### Power calculation

Based on Swiss findings regarding the effect of ASSIP [17], we anticipate that 10% of individuals in the group receiving ASSIP plus conventional treatment, and 20% of individuals receiving conventional treatment alone, will attempt suicide again during the follow-up period. According to the chi-square test, 199 individuals are required in each group to achieve a significant difference with a power of 0.8 and an alpha value of 0.05. Assuming a 15% dropout rate among patients, 460 patients need to be recruited. If the dropout rate is lower, fewer patients will suffice.

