### Study design and data management

The study is an RCT. Patients are randomized to either receive ASSIP + usual treatment or only usual treatment. The project employs stratified randomization based on the study site, ensuring that 50% of patients receive ASSIP at all sites. Randomization occurs electronically at the end of visit 1 via REDCap and is blinded to the data handler. REDCap is an electronic data capture tool [21] hosted at Lund University which will be used to manage data collection. The participating regions will collectively recruit a total of up to 460 patients who have recently attempted suicide. For this study, a suicide attempt is operationally defined as a self-inflicted, potentially harmful behavior exhibiting explicit or implicit evidence of the individual’s intent to die [22].

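### 460 recruits less the stated 15% dropout leaves 391 evaluable patients, slightly under the 398 the protocol requires: a minor error of wording, worth about 0.7 points of power at worst

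*Protocol article*

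**What the plan says.** The Power calculation section of the protocol article sets the planning rates. It expects a new attempt in 10% of the ASSIP arm; for the control arm the figure reads: "20% of individuals receiving conventional treatment alone, will attempt suicide again during the follow-up period". From these it derives the evaluable number: "According to the chi-square test, 199 individuals are required in each group", with "a power of 0.8 and an alpha value of 0.05". It then adds the allowance for loss: "Assuming a 15% dropout rate among patients, 460 patients need to be recruited". The section closes by noting that a smaller number is enough if dropout turns out lower. It does not show how the allowance was applied, and it does not say what a dropout is lost to (the interview or the primary analysis).

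Two other places bear on the point. The Study design and data management section gives 1:1 allocation ("ensuring that 50% of patients receive ASSIP at all sites") and treats the same total as a ceiling: "The participating regions will collectively recruit a total of up to 460 patients who have recently attempted suicide". The Outcomes section builds the primary outcome from telephone interviews, medical charts and national registers combined, and counts an attempt found in any of them.

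**The concern.** A sample size of 398 evaluable patients and a 15% loss together fix the number to recruit. That number is 398 divided by 0.85, which is more than 460. Taken literally, the section does not deliver the evaluable number that it has just called necessary, and 199 per group is the minimum for 80% power, so there is no margin to absorb the gap. Because 460 is also the recruitment ceiling, no permitted enrolment reaches 398 at the assumed dropout.

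What is at stake is the accuracy of the stated power, and the use of the closing remark on lower dropout while recruitment is under way. A team seeing 14% dropout could read it as leave to stop short of 460, when 460 would not quite be enough.

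**Working it through.** **Inputs, all from the Power calculation section unless noted:** event rates 20% (usual treatment) and 10% (ASSIP plus usual treatment); chi-square test; power 0.80; alpha 0.05; 15% dropout; 460 recruited; 1:1 allocation (Study design and data management). Sidedness is not stated. Two-sided is assumed because it reproduces the protocol's figure.

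**Step 1: reproduce 199 per group.** Pooled two-proportion formula without continuity correction, with mean rate p̄ = 0.15:

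n = [1.960 × √(2 × 0.15 × 0.85) + 0.8416 × √(0.20 × 0.80 + 0.10 × 0.90)]² / (0.20 − 0.10)²

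= [0.9897 + 0.4208]² / 0.01 = 1.9896 / 0.01 = 198.96, so 199 per group and 398 in total. This matches exactly. Other variants do not: 219 with continuity correction, 157 one-sided, 197 with unpooled variance, 195 by arcsine.

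**Step 2: apply the 15% loss.**

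- Recruits needed: 398 / (1 − 0.15) = 468.2, so 469. By arm, 199 / 0.85 = 234.1, so 235 and a total of 470.
- Evaluable from 460: 460 × 0.85 = 391, or 195.5 per arm. This is 398 − 391 = 7 short (1.8%).
- Largest loss that 460 can absorb: 1 − 398/460 = 62/460 = 0.1348, about 13.5%.

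**Step 3: power at the resulting numbers** (same formula solved for power, 20% against 10%):

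| Evaluable per arm | Meaning | Power |
|---|---|---|
| 195.5 | 460 recruited, 15% lost to the primary analysis | 79.3% |
| 199 | the number the protocol requires | 80.0% |
| 230 | all 460 analysed | 85.4% |

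**Step 4: where 460 may have come from.** Multiplying gives 398 × 1.15 = 457.7, so 458. By arm, 199 × 1.15 = 228.9, so 229. Either reaches 460 only after rounding up (to 230 per arm).

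**Step 5: the remark on lower dropout.** Recruits needed for 398 evaluable:

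- at 14% dropout, 398 / 0.86 = 462.8, so 463 (more than 460)
- at 10%, 398 / 0.90 = 442.2, so 443
- at 5%, 398 / 0.95 = 418.9, so 419

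The remark is true below about 13.5% and fails only between there and 15%.

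**The case against.** The best defence has four parts.

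*The size is negligible.* A gap of 0.7 points of power, or about 2% of recruits, is far inside the uncertainty of round planning rates. With the ASSIP rate held at 10%, a control rate of 20.1% restores 80% power at 195.5 per arm. At the full 199 per arm, a control rate of 19% gives 72% and 21% gives 86%. This stands, and it is why the point is minor.

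*The shortfall may not occur.* Dropout is not defined, and the Outcomes section takes the primary outcome from charts and linked registers as well as interviews. A patient who misses the interviews can still contribute. Some withdrawals might remove linked data too, so the evaluable number lies somewhere from 391 to 460. This also stands: 391 is the worst case.

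*The cause is not shown.* A reader might infer that the authors multiplied by 1.15 where they should have divided by 0.85. That is the likeliest route, but the article gives no formula, and multiplication yields 458, not 460, without a further rounding. It remains an inference. The shortfall does not depend on it, since 460 × 0.85 is below 398 however 460 was reached.

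*The closing remark is conditional.* A reader might take it to claim slack at the assumed 15%, and want it struck out. It makes no such claim, and it is correct for any dropout below about 13.5%. It needs a threshold, not deletion.

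None of this makes the sentence on 460 correct. With 15% lost to the analysis, it does not give the 398 stated just before it.

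**Conclusion.** The concern holds as a minor inconsistency. The figures in the Power calculation section do not agree with each other: 460 recruits with 15% lost give 391 evaluable and 79.3% power, against the 398 and 80% stated, and full cover for that loss would need 469 or 470.

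This rests on a two-sided chi-square test without continuity correction (the version that reproduces 199), on loss spread evenly over the arms, and on every dropout being lost to the primary analysis. If instead nobody is lost to it, and the 10% and 20% rates apply to all randomised patients, power is about 85%. The printed 80% corresponds to neither case exactly.

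A reader might infer that the trial is materially underpowered or must enrol more patients. The documents do not support that: the worst-case loss is 0.7 points, and the chart and register sources may remove it altogether.

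**What to change.** Restate the figures in the Power calculation section and leave enrolment at 460. Suggested wording: *With 460 recruited and 15% lost to the primary analysis, 391 are evaluable and power is about 79%; 80% power holds for dropout up to about 13.5%.*

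If all randomised patients are to be analysed through charts and registers, add: *With all 460 analysed (230 per arm), power is about 85% at 10% against 20%.* Either way, say whether dropout means loss to the interview or loss to the primary analysis.

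Keep the remark that fewer patients are enough at lower dropout, but tie it to dropout below 13.5%.

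The cost is a sentence or two and, in the worst case, a stated power of 79% in place of 80%. Recruitment, conduct and analysis do not change.

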### Mapping the implementation of ASSIP

Method adherence to the project is assessed by ensuring that each component of ASSIP has been implemented [19], and when implemented, it is recorded in a web-based application for electronic data collection in research studies. In collaboration with the creators of ASSIP, a scale has been developed to assess the adherence and competence of the therapists, ASSIP adherence and competence scale (ASSIP ACS) [33]. All therapists self-rate after each ASSIP session and overall method adherence will be rated by an independent rater who will review a random sample (10%) of all therapy sessions.

### Mapping of treatment as usual

TAU is mapped through telephone interviews and journal reviews using a specific template and recorded in REDCap. The mapping includes ICD-10 diagnoses, healthcare contacts, pharmacological and psychotherapeutic treatments, as well as other interventions.

### Statistical considerations

The chi-square test will be utilized to assess differences between the intervention group and the control group regarding the main outcome. The Wilcoxon signed-rank test is planned to be used to analyze significant changes over time, and the Mann-Whitney U test for differences between groups. To visually represent the cumulative probability of suicide reattempt over time in each treatment group, we plan to create Kaplan-Meier curves. Simple and multiple logistic regression to compare the relative impact of different factors on the outcome. Data regarding the professions and previous psychotherapeutic training of therapists will be collected and investigated as putative moderators. Further, we plan to employ cost calculation items for assessing direct and indirect costs, and total costs for the cost-effectiveness model.

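### Free improvement: the between-arm tests named in the protocol use neither the randomisation stratum nor the baseline scores; the cost in power is small for suicide attempts and larger for the continuous scales

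*Protocol article*

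**What the plan says.** The protocol article, Statistical considerations, names the test for suicide attempts: "The chi-square test will be utilized to assess differences between the intervention group and the control group regarding the main outcome". For the remaining measures it says: "The Wilcoxon signed-rank test is planned to be used to analyze significant changes over time, and the Mann-Whitney U test for differences between groups". Neither sentence mentions a stratum or covariate. The same section plans Kaplan-Meier curves for display, without a log-rank or Cox analysis. It also plans simple and multiple logistic regression, but to weigh different factors against each other and not as the stated comparison of the arms.

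Three other places matter:
- **Study design and data management:** "The project employs stratified randomization based on the study site, ensuring that 50% of patients receive ASSIP at all sites".
- **Table 2:** MADRS-S, EQ-5D-5L, ISMI and ISSI are collected at baseline and at 3, 12 and 24 months.
- **Aims:** reduction of self-stigma, which ISMI measures, is listed among the primary research questions.

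Under Outcomes, the secondary outcome (suicidal ideation) is binary, defined by a cut-off of 4 on MADRS-S item 9. New attempts are counted from interviews, charts or registers.

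**The concern.** When randomisation is stratified, the usual practice is to carry the stratum into the comparison. When an outcome scale is also measured at baseline, the between-arm comparison is normally adjusted for that value. Both use data the trial already holds. The named tests do neither, so the trial may reach less power than its sample size could give.

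There is also a point of interpretation. A signed-rank test of change within one arm does not compare the arms. Participants enter within three months of a suicide attempt, so improvement in both arms is plausible. A significant change within the ASSIP arm could then be read as an effect of ASSIP.

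**Working it through.** **1. The plan's own figure.** Inputs from Power calculation: "we anticipate that 10% of individuals in the group receiving ASSIP plus conventional treatment, and 20% of individuals receiving conventional treatment alone", and "199 individuals are required in each group to achieve a significant difference with a power of 0.8 and an alpha value of 0.05". With the two-sided pooled-variance formula, n = [1.960 × √(2 × 0.15 × 0.85) + 0.842 × √(0.20 × 0.80 + 0.10 × 0.90)]² / 0.10² = (0.990 + 0.421)² / 0.01 ≈ 199 per group. This matches exactly.

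For dropout: "Assuming a 15% dropout rate among patients, 460 patients need to be recruited". Dividing, 398 / 0.85 = 468.2, so 469; the stated 460 is within 3%. If 15% of 460 are lost, 391 remain (195.5 per group) and chi-square power is 79.3%. The planned test therefore meets its target to within a point.

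**2. Attempts: adding site or a baseline covariate.** Simulated with 398 analysed and 10% versus 20%. Assumed, because the documents do not give them: six sites, the between-site variation, and the strength of the covariate.

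| Assumption | Chi-square | Adjusted analysis |
|---|---|---|
| Site SD 0 (logit scale) | 81.3% | 81.1% (Cochran-Mantel-Haenszel) |
| Site SD 0.3 | 81.2% | 81.4% |
| Site SD 0.5 | 79.8% | 80.3% |
| Site SD 0.8 | 82.6% | 84.6% |
| Covariate AUC 0.64 | 81.2% | 81.9% (logistic) |
| Covariate AUC 0.70 | 80.7% | 82.8% |
| Covariate AUC 0.74 | 80.5% | 84.1% |

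Under no treatment effect the chi-square rejected in 4.0% of trials, so it is valid and slightly conservative. Simulation error across these runs is about 0.5 to 0.9 points. A single yes/no covariate such as prior attempts would probably sit toward the lower end of the AUC range.

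**3. Attempts: using event times.** With 398 followed completely, the chi-square gives 81.3% and the log-rank 81.2%: no gain. With 460 randomised and 15% lost at uniformly distributed times:

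| Analysis | Constant hazard | Front-loaded hazard |
|---|---|---|
| Chi-square, completers only | 79.9% | 79.7% |
| Log-rank, dropouts censored | 83.4% | 84.0% |
| Chi-square, outcome known for all 460 | 85.9% | 85.2% |

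The log-rank gains 83.4 − 79.9 = 3.5 and 84.0 − 79.7 = 4.3 points over a completers-only test.

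**4. Continuous scales.** Baseline adjustment multiplies the residual variance by 1 − ρ², where ρ is the baseline to follow-up correlation. From 80% power, adjusted power is Φ[(1.960 + 0.842)/√(1 − ρ²) − 1.960]. That gives 83.6% at ρ = 0.3, 89.9% at 0.5 and 93.8% at 0.6. A simulation with 398 analysed and an assumed effect of 0.281 SD compared the rank methods directly:

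| ρ (assumed) | 1 − ρ² | Mann-Whitney | Baseline-adjusted rank ANCOVA |
|---|---|---|---|
| 0.3 | 0.91 | 78.1% | 81.9% |
| 0.5 | 0.75 | 78.1% | 87.4% |
| 0.6 | 0.64 | 79.1% | 91.6% |

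The protocol does not say whether the Mann-Whitney test is applied to follow-up scores or to change scores. If to change scores, the variance factor is 2(1 − ρ): 1.4, 1.0 and 0.8 at these correlations. This always exceeds 1 − ρ², because the difference is (1 − ρ)². Baseline adjustment is the more efficient choice on either reading.

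**5. Binary ideation.** With an assumed 25% in controls and the same underlying effect, chi-square against baseline-adjusted logistic regression gives 49.2% and 49.8% at ρ = 0.3, 49.8% and 55.0% at 0.5, and 50.2% and 59.6% at 0.6.

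**The case against.** The strongest case against has four parts.

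- **The primary test does what it was planned to do.** It is valid and reaches about 80% power. This stands. A reader might infer that omitting the stratum makes the test invalid or the trial underpowered; the calculations support neither.
- **The largest primary figure, 85% to 86%, does not come from a better test.** It comes from having an outcome for all 460, and the chi-square itself attains it. A reader might infer from the 15% allowance that dropouts will be excluded. The protocol does not say so: the allowance only sets the recruitment target, and Outcomes accepts an attempt from any source. Nor can records be assumed to replace every lost interview, since Background estimates that only about half of attempts receive hospital care. So 85% to 86% is an upper bound, and the log-rank gain is conditional on loss.
- **The gain on the scales might be carried over to the secondary outcome.** That is not supported: ideation is binary and gains less. Nor does the Wilcoxon test ignore baseline. It is paired and uses it; its limit is that it makes no comparison between arms, and the protocol does not claim that it does.
- **Logistic regression is already planned, and an article leaves covariates to the analysis plan.** This is fair, and an unseen plan may already adjust. But the article does name its between-arm tests, and the regression is given a different purpose. The point concerns the tests as stated.

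**Conclusion.** The point holds as an efficiency improvement at almost no cost, not as an error. For attempts at 24 months the gain is modest: about 0 to 2 points from site, 1 to 4 from a baseline covariate, and 3 to 4 from event times only if 15% are lost and would otherwise be left out. The worthwhile gain is on the continuous scales, self-stigma among them: from about 78% to about 82%, 87% and 92% at correlations of 0.3, 0.5 and 0.6. In sample-size terms that is 1/0.91, 1/0.75 and 1/0.64, or about 10%, 33% and 56% more participants.

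The number of sites, site variation, covariate strength, correlations, scale effect, control ideation rate and dropout timing are all assumptions. The direction for the scales does not depend on them; the size does.

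**What to change.** - **Attempts:** make the treatment-effect analysis a Cochran-Mantel-Haenszel test by site, or a logistic regression with site (small sites pooled) and prior-attempt history. Include all randomised participants in their allocated arm. Report the risk difference and odds ratio with 95% confidence intervals.
- **Event times:** add a site-stratified log-rank or Cox analysis to the planned Kaplan-Meier curves.
- **Scales:** replace Mann-Whitney with a baseline-adjusted comparison, either a mixed model over 3, 12 and 24 months or ANCOVA, with site included.
- **Ideation:** adjust the binary outcome for its baseline value.
- **Within-arm Wilcoxon tests:** keep as descriptive only.

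The cost is analysis-plan wording and slightly more analysis work; no further data are needed. Timing needs care. Under Outcomes, the research team plans its own interim analyses of safety and effectiveness without a formal monitoring committee. The change should therefore be fixed and dated before anyone deciding it reviews unblinded outcome data, so that it cannot appear data-driven.

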### Reporting and publication plan

In accordance with the Declaration of Helsinki, study results will be made publicly available, through publication and/or a public database as soon as possible after the study is completed. This applies regardless of whether the results are positive, negative, or neutral. The first main outcome study will provide preliminary results after a one-year follow-up is completed for the last participant included in the RCT.

## Discussion

This large-scale Swedish intervention study, conducted as an RCT, aims to investigate the effects of a brief psychotherapeutic intervention known as ASSIP within psychiatric services for individuals who have recently attempted suicide. The study design is poised to offer novel insights not only into the direct impact of ASSIP on reducing suicide attempts but also into a wide array of potential mediators and moderators. These include various aspects of mental health, therapeutic alliance, coping strategies, social support networks, experiences of stigma, sick leave patterns, and the specific components of the ASSIP intervention.

Should this suicide prevention intervention trial yield positive outcomes, it stands to build upon prior research findings related to the prevention and treatment of individuals who have recently attempted suicide, potentially elucidating the underlying mechanisms of action of ASSIP.

Through this comprehensive approach, our study endeavours to provide valuable insights into the efficacy factors that influence outcomes, the cost-effectiveness of ASSIP, and its potential benefits across diverse patient populations. Ultimately, our research aims to advance the understanding of psychotherapeutic interventions for suicide prevention.

## Data Availability

No datasets were generated or analysed during the current study.

## Abbreviations

ASSIP: Attempted Suicide Short Intervention Program
ASSIP-ACS: Attempted Suicide Short Intervention Program - Adherence and Competence Scale
AUDIT: Alcohol Use Disorders Identification Test
C-SSRS: Columbia-Suicide Severity Rating Scale
COPE: Coping Orientation to Problems Experienced
DSM-5: Diagnostic and Statistical Manual of Mental Disorders, 5th Edition
DUDIT: Drug Use Disorders Identification Test
EQ-5D-5L: EuroQol 5-Dimension 5-Level
ICD-10: International Classification of Diseases, 10th Revision
ISMI: Internalized Stigma of Mental Illness
ISSI: Interview Schedule for Social Interaction
LEC-5: Life Events Checklist for DSM-5
LISA: Longitudinal Integrated Database for Health Insurance and Labour Market Studies
MADRS-S: Montgomery-Åsberg Depression Rating Scale - Self Report
MINI: Mini International Neuropsychiatric Interview
RCT: Randomized Controlled Trial
SCB: Statistics Sweden (Statistiska centralbyrån)
SIS: Suicide Intention Scale
TAU: Treatment As Usual
WAI-SR: Working Alliance Inventory - Short Revised
